**Cases**	
• Aged 15 years or above • Resident in the catchment area • ICD-11 primary psychotic disorder • Not treated with antipsychotic medication for ≥ 1 continuous month • Onset within 2 years	• Moderate or severe neurodevelopmental disability (e.g. intellectual disability) • Clinically manifest organic cerebral disorder • Transient psychotic symptoms resulting from acute intoxication
**Matched controls**	
• Aged 15 years or above • Resident in the catchment area • Same gender as index case • Age within 5 years of index case	• Past or current psychotic disorder • Moderate or severe learning disability • Clinically manifest organic cerebral disorder
**Relatives**	
• Aged 15 years or above • Relative or carer for a person with psychosis recruited into the study	• Insufficient contact with person with psychosis to provide information on family burden and mental health

In addition, in the Addis Ababa sub-cities we will identify people with untreated psychosis who are homeless. Our operationalisation of the concept of homelessness was informed by stakeholders in the community advisory board. Homelessness is thus defined here as spending the night unsheltered or in other places not intended for habitation (e.g. under bridges). It includes people who can sporadically pay for shelter but excludes people who spend their days on the streets, for example, to beg, but who have stable night-time accommodation. The methodology used for the homeless sample will necessarily differ from the main epidemiological study (as outlined below) but will allow quantification of the proportion of people with untreated psychosis in Addis Ababa who are homeless. On the basis of our previous work, we expect 31 homeless people to have untreated psychosis on initial case-finding (cross-sectionally) with further incident cases recruited over time [92]. See Fig 2 for samples in the different components of the epidemiological study.

**Fig 2 pone.0293232.g002:**
[figure not shown]
Samples for epidemiological studies.

#### Sample size

*Incidence*. With a conservative estimate of the population at risk (≥15 years) of 741,936 (rural population of 713,123 with an estimated 62% aged 15 years or above, and an urban population of 416,389 in 2016 with an estimated 72% aged 15 years or above) screened for incident cases over two years, assuming an incidence of psychosis of 18.7/100000 [88] person-years in the rural setting, this amounts to 139 new cases per year and approximately 554 people with psychosis including those who developed psychosis in the two years preceding baseline. Assuming 70% are identifiable and eligible, we expect to identify around 390 people with psychosis meeting our inclusion criteria. This sample size will have 80% power to detect an incidence rate ratio (IRR) of around 1.6 for urban exposure, in keeping with studies from high-income countries [89], and for males vs. females [88].

*Factors associated with onset of psychosis (case-control)*. For a sample size of 390 people with psychosis and 390 controls, 16% early khat use in controls [39], we will have 80% power to detect an odds ratio of 1.7 for increased odds of early khat use in people with psychosis with p = 0.05.

*Follow-up study*. Assuming 20% loss to follow-up, we will have 80% power (p = 0.05) to detect a risk difference of 18% in receipt of minimally adequate care (medication prescription and attending for 4 follow-up appointments over 12 months [93]) assuming 30% receipt of minimally adequate care in non-khat chewers [94].

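### The stated 80% power at an incidence rate ratio of about 1.6 does not follow from 390 cases: a plain Poisson comparison gives over 99% power at 1.6 and reaches 80% at about 1.33

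*Protocol article*

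**What the plan says.** Under Aim 2, Sample size (Incidence), the protocol article starts from a "conservative estimate of the population at risk (≥15 years) of 741,936". The rural part of this is a "rural population of 713,123 with an estimated 62% aged 15 years or above"; the urban part is taken as 72% of 416,389 residents. It proceeds by "assuming an incidence of psychosis of 18.7/100000 [88] person-years in the rural setting", and reports that "this amounts to 139 new cases per year and approximately 554 people with psychosis", a total that includes onsets in the two years before baseline. It takes 70% of these as identifiable and eligible, so that "we expect to identify around 390 people with psychosis meeting our inclusion criteria".

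The next sentence is the power claim: "This sample size will have 80% power to detect an incidence rate ratio (IRR) of around 1.6 for urban exposure". The same sentence then makes the claim for men compared with women, citing earlier studies for both contrasts. The count it points back to is the 390 just derived.

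The paragraph gives no alpha, design effect or other variance allowance for this comparison. The Data analysis section names Poisson regression for incidence rates and does not mention overdispersion. The two contrasts are the incidence hypotheses (2a) under Hypotheses.

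**The concern.** In a comparison of two incidence rates, power depends on the number of events, their split by person-time, the ratio and alpha. The paragraph supplies the event count, the rural/urban split and the ratio. With 390 events, a ratio of 1.6 is far from the edge of what a simple Poisson comparison can detect, so 80% looks much too low.

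The mismatch bears on both incidence hypotheses. It leaves the reader unsure which cases enter the incidence analysis: all 390, or only those with onset during surveillance. It also leaves unclear whether an unstated variance allowance lies behind 1.6. If one does, the model named for the analysis does not match it.

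**Working it through.** **Inputs from the Sample size section.** Rural person-time share: 713,123 × 0.62 = 442,136. Urban: 416,389 × 0.72 = 299,800. Total: 741,936. Urban share a = 299,800 / 741,936 = 0.404. Incidence 18.7 per 100,000 person-years; 70% identifiable and eligible; ratio R = 1.6; target power 80%.

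**Assumptions.** Two-sided alpha 0.05: none is stated for incidence, and the other two calculations in the section use p = 0.05 without giving sidedness. Male share of person-time a = 0.5: the document gives no figure.

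**Step 1. The case count reproduces.** 741,936 × 18.7/100,000 = 138.7 per year; × 4 onset-years = 555; × 0.70 = 388. The plan has 139, about 554 and around 390.

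**Step 2. Power at 1.6 with D = 390.** The expected share of cases in the higher-rate group is q = aR / (aR + 1 − a). SE(ln R) = √[1/(Dq) + 1/(D(1 − q))]. Power = Φ(ln R / SE − 1.960), with ln 1.6 = 0.470.

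- Urban vs rural: q = 0.520, giving 203 and 187 cases; SE = 0.1014; 0.470/0.1014 = 4.64; power = Φ(2.68) = 99.6%.
- Men vs women: q = 1.6/2.6 = 0.615, giving 240 and 150 cases; SE = 0.1041; 0.470/0.1041 = 4.52; power = Φ(2.56) = 99.5%.

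An exact conditional binomial test gives 99.5% and 99.6%.

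**Step 3. Cases needed for 80% power at 1.6.** D = (1.960 + 0.842)² / [(ln 1.6)² q(1 − q)] = 35.5 / [q(1 − q)]. Urban vs rural: 35.5/0.2496 = 142. Men vs women: 35.5/0.2367 = 150.

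**Step 4. Ratio detectable with 80% power.** Solve ln R = 2.802 × SE. The number of onsets inside the two-year window is 741,936 × 18.7/100,000 × 2 × 0.70 = 194.

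| Cases | Urban vs rural | Men vs women |
|---|---|---|
| 390 | 1.33 | 1.33 |
| 194 | 1.50 | 1.51 |

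**Step 5. Does another alpha rescue 1.6?** With 390 cases, alpha 0.01 gives 1.41 to 1.42 and alpha 0.001 gives 1.52 to 1.53. A one-sided 0.05 test gives 1.29. None reaches 1.6.

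**Step 6. Variance inflation that would reconcile the figures.** Urban vs rural: 390/142.4 = 2.7, or 194/142.4 = 1.4. Men vs women: 390/150.1 = 2.6, or 194/150.1 = 1.3.

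**Step 7. What between-area variation could do to the urban contrast.** Setting lists seven rural districts and two sub-cities. Weighting areas equally within each group, add CV² × (1/2 + 1/7) to SE², where CV is the between-area coefficient of variation of the rate. The document gives no CV, so a range is shown.

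| Assumed CV | Detectable ratio, 390 cases | Detectable ratio, 194 cases |
|---|---|---|
| 0 | 1.33 | 1.50 |
| 0.10 | 1.44 | 1.59 |
| 0.15 | 1.55 | 1.69 |
| 0.20 | 1.70 | 1.83 |

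With 390 cases, a CV of about 0.16 to 0.17 brings the detectable ratio to about 1.6.

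**The case against.** The strongest defence concerns the urban contrast. Residence is an exposure of whole areas, with two on one side and seven on the other. Step 7 shows that moderate between-area variation alone would move the detectable ratio from 1.33 to about 1.6. A condensed article may leave such an allowance to a fuller document. This stands to the extent that 1.33 cannot simply replace 1.6 for urban versus rural. It does not rescue the sentence: the claim is attached to 390 cases with no allowance, the named model is plain Poisson, and the same 1.6 is given for men versus women, a contrast within areas to which the argument does not apply.

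A second defence is that only onsets inside the surveillance window may count. The gap is then 1.5 against 1.6, which is modest. But the sentence refers to the 390, not to about 194.

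Two stronger readings are tempting and are not supported:

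- A reader might infer that power was computed on one year's 139 cases, since that count gives a detectable ratio of about 1.61 to 1.63. The protocol does not say so, and 150 cases in a single stratum split by sex would fit 1.6 equally well. The origin of the figure is unknown.
- A reader might infer that the plan puts ratios below 1.6 out of reach, so that a null result would be misread. The section states power at one value, tied to earlier studies, and Data analysis reports rates with 95% confidence intervals. A null result would be judged from its interval.

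**Conclusion.** The concern holds as an error in a stated figure. Under the plain Poisson comparison, 390 cases give 99.5% to 99.6% power at 1.6, not 80%. The 80% detectable ratio is about 1.33, and 1.6 needs 142 to 150 cases. This rests on two-sided alpha 0.05 and, for sex, on equal person-time. No alpha down to 0.001 changes the conclusion.

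The error is conservative: power is understated for the stated count, and the study is not shown to be too small. For men versus women the correction is direct. For urban versus rural, 1.33 (or 1.5 with 194 cases) is the value with no between-area variation and should not be read as what the study will achieve. The CVs used to show this are illustrative.

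**What to change.** Rewrite the sentence to give the number of cases entering the incidence analysis, the alpha with its sidedness, and any inflation factor, together with the ratio these produce.

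- Men versus women: about 1.33 if all 390 cases are analysed, or about 1.5 if only the roughly 194 onsets inside the two-year window are.
- Urban versus rural: give the same values, labelled as assuming no between-area variation. If 1.6 was meant to allow for such variation, state the inflation (about 2.7 with 390 cases, about 1.4 with 194) and replace plain Poisson regression for this contrast with an overdispersed or area-level model.

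The cost is one corrected sentence and, if the allowance was intended, one change to the named model. Recruitment targets and design are unaffected.

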Khat use: Khat leaves contain *Catha Edulis*, an amphetamine-like substance [36]. Khat is widely used across the Horn of Africa and its diaspora [37,38]. In Ethiopia, use is increasing, with 15.8% nationally reporting current use [39], but over 50% of adults in some districts [40] and high levels in students [41]. In a case-control study from Somalia, age of onset of khat use was associated with clinical ratings of current psychotic symptoms [42], indicating a potential role as a risk factor for onset of primary psychosis. However, the relationship between culturally relevant patterns of khat use [43] and incidence and early course of psychoses has not been investigated.Trauma: In studies conducted in high-income countries, co-morbidity of post-traumatic stress disorder (PTSD) in people with psychosis ranges from 13–55% [44]. Exposure to traumatic events is a risk factor for developing psychosis [45] and associated with poorer outcomes [46]. In LMICs, traumatic experiences are prevalent among the general population, with an estimated 8% affected by PTSD [47]. In people with psychosis, traumatic experiences are likely to be more common, arising from restraint or coercive treatments [7], accidents or sexual assault [7] or other forms of violent victimisation [22]. The limited evidence available about the role of traumatic exposures in onset and course of psychosis in LMICs indicates variation of the association across setting [48].Family communication and involvement: High ‘expressed emotions’ from family members, specifically hostility, critical comments and over-involvement, are associated with increased risk of relapse and hospitalisation of people with psychosis [49]. However, a recent meta-analysis [50] identified only one study of expressed emotion from Africa [51]. Important cultural variability of expressed emotion is recognised [50,52]. Given the crucial role of the family in caregiving in Ethiopia and other African countries [53], local evidence is urgently needed on relevant family communication patterns to inform intervention.Personal recovery: Defined as *“a way of living a satisfying, hopeful and contributing life even within the limitations caused by illness” [54],* personal recovery is increasingly recognised as an essential goal for intervention [55]. However, the need to explore applicability of this concept in non-Western populations has been noted [56]. A study from Ethiopia explored the concept of recovery in an urban, hospital-based study [57]. However, evidence from a representative sample is required to ensure innovations are based on priorities and values of people with psychosis.

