### Hypotheses

(2a) Incidence study

Incidence of psychosis will be higher in men [88] and in urban residents [89].

(2b) Case-control study

Earlier age of khat initiation and/or problematic khat use [42], exposure to traumatic events prior to psychosis onset and childhood adversity [45] will be associated with increased odds of psychosis

(2c) Cohort study

Maladaptive family interactions [50], exposure to traumatic events [46,90], physical co-morbidity, and poverty will be associated with poorer 12-month clinical, functional and personal recovery, after adjusting for confounders.

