#### Sample

We will recruit people with untreated psychosis (rural n = 240; urban n = 150), relatives (rural n = 240; urban n = 150) and age- and gender-matched population controls (rural n = 240; urban n = 150). Eligibility criteria will be identical to those detailed in the published INTREPID protocol [9] with an additional requirement that onset of psychosis was within the past two years, and extending the lower age to 15 years and removing an upper age limit (see Table 1). The reason for lowering the age for inclusion is because many cases of psychosis start in late adolescence [91]. We will seek informed consent from those aged under 18 years. If they are an emancipated minor, we will not seek permission from a guardian/responsible family member. If they are aged 15–17 years and not an emancipated minor, we will seek permission from that person before including in the study.

**Table 1 pone.0293232.t001:** Eligibility criteria for SCOPE epidemiological study.

Inclusion criteria	Exclusion criteria

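### The case-control power rests on 16% early khat use, but the Introduction gives the same reference as 15.8% current use, so 80% power at an odds ratio of 1.7 is unsupported for early initiation

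*Protocol article*

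**What the plan says.** The Sample size section of the protocol article (Aim 2, case-control paragraph) assumes, for 390 cases and 390 controls: "16% early khat use in controls [39], we will have 80% power to detect an odds ratio of 1.7". The claim in full is "80% power to detect an odds ratio of 1.7 for increased odds of early khat use in people with psychosis with p = 0.05". So the word early is attached both to the control prevalence and to the effect to be detected.

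The khat paragraph of the Introduction cites the same reference: "In Ethiopia, use is increasing, with 15.8% nationally reporting current use [39], but over 50% of adults in some districts [40".

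Under Hypotheses, the exposures listed for the case-control study are: "Earlier age of khat initiation and/or problematic khat use [42], exposure to traumatic events prior to psychosis onset and childhood adversity [45". Current khat use is not among them. The article gives no age that defines early use and no prevalence for it.

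**The concern.** Current use and early use are different exposures. Current use counts people who chew khat now, whatever age they started. Early use counts people by the age at which they started, whether or not they still chew. The article attributes both to one reference, and the two figures agree after rounding (15.8% and 16%). This suggests that a current-use prevalence was entered under an early-use label.

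The detectable odds ratio in a case-control study depends strongly on how common the exposure is among controls. This is the only power statement for the case-control hypotheses, and the Abstract names khat among the potential aetiological factors. If the khat result is null, readers will judge it against a claimed 80% power at an odds ratio of 1.7. That claim needs an input that describes the exposure being tested.

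**Working it through.** **Inputs.** 390 cases and 390 controls, control prevalence p0 = 16%, odds ratio 1.7, significance level 0.05 (all from Sample size). Sidedness is not stated. Two-sided is assumed because it fits the claim; a one-sided test would give 90.4%.

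**Formulas.** Exposure in cases: p1 = p0·OR / (1 − p0 + p0·OR). With p̄ = (p0 + p1)/2 and n = 390 per group, power = Φ{[(p1 − p0) − 1.96·√(2p̄(1 − p̄)/n)] / √([p0(1 − p0) + p1(1 − p1)]/n)}. The continuity-corrected version also subtracts 1/n from the difference.

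**Reproducing the stated figure.**
- p1 = 0.16 × 1.7 / (0.84 + 0.272) = 0.272 / 1.112 = 0.2446
- difference = 0.0846; p̄ = 0.2023
- null standard error = 0.02877; alternative standard error = 0.02861
- uncorrected: (0.0846 − 1.96 × 0.02877) / 0.02861 = 0.99, power 83.8%
- corrected: (0.0846 − 0.0026 − 0.0564) / 0.02861 = 0.90, power 81.5%

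The odds ratio detectable with 80% power is 1.66 uncorrected and 1.68 corrected, and both round to 1.7. A matched-pair calculation with no within-pair correlation gives 83.5%. The stated claim therefore reproduces for a 16% exposure. Entering 15.8% gives 83.5% (81.1% corrected), so the claim is equally consistent with the current-use figure having been used.

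**Dependence on the input.** The article gives no early-use prevalence, so the range below is an assumption. It uses n = 390 per group, two-sided 0.05; continuity-corrected values are in brackets.

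| Early use in controls (assumed) | Exposure in cases at OR 1.7 | Power at OR 1.7 | OR detectable with 80% power |
|---|---|---|---|
| 5% | 8.2% | 43.9% (38.3%) | 2.19 (2.26) |
| 8% | 12.9% | 60.6% (56.0%) | 1.92 (1.97) |
| 10% | 15.9% | 68.8% (65.0%) | 1.82 (1.86) |
| 14% | 21.7% | 80.1% (77.3%) | 1.70 (1.73) |
| 16% | 24.5% | 83.8% (81.5%) | 1.66 (1.68) |
| 25% | 36.2% | 92.4% (91.3%) | 1.56 (1.57) |

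Power at 1.7 falls below 80% once control prevalence drops under about 14% uncorrected, or slightly above 15% corrected. The margin below 16% is small; above 16%, power rises.

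**The case against.** The best defence is that nothing has been miscalculated and no loss of power has been demonstrated. Both parts of that stand.

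A reader might infer that early users are a subset of current users, so that 16% must be too high and the test must fall well short of 80%. The documents do not support this. People who started early are a subset of people who ever used khat, and some may have stopped. The 15.8% is national, while the same paragraph reports more than half of adults using khat in some districts and high levels among students. The controls are also not a national sample: they are "age- and gender-matched population controls (rural n = 240; urban n = 150", drawn from the neighbourhoods of cases. The direction of any error is unknown.

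A reader might also infer that the claim holds only if every current user started early. That is too strict. An early-use prevalence of about 14% already gives 80% uncorrected, whoever makes up that 14%.

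Three further points carry weight. One reference can report two quantities, and the source cannot be checked here. The 390 cases come from expected case yield (about 554 × 70%), not from this calculation. The age cut-off and the coding of the khat exposure may be set in the full protocol or analysis plan, and problematic use is already in the hypothesis and measured in cases and controls.

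The inconsistency remains. It is not a detail left out for brevity: the article states an input and attributes it to a source that it describes differently elsewhere.

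**Conclusion.** The point holds as a mislabelled or unsourced input. The article's own description of the reference does not support 16% as a prevalence of early khat use, so the 80% power at an odds ratio of 1.7 is unsupported for earlier age of initiation. It would be wrong to call the study underpowered for khat. Over assumed control prevalences of 5% to 25%, uncorrected power at 1.7 runs from 44% to 92% and the detectable odds ratio from 2.19 to 1.56. These figures assume a two-sided 0.05 test, 390 per group and an unadjusted comparison.

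That the inconsistency exists is certain. That the 16% is the rounded current-use figure is likely but not proven. Whether power is lower or higher than claimed cannot be settled from the article. This is a should-fix: the correction is cheap and affects how a khat result will be read, but no recruitment target depends on it.

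**What to change.** State what the 16% measures. Either label it as current use, or replace it with a sourced prevalence of early use together with the age cut-off that defines early, fixed before analysis. If it is relabelled as current use, say plainly that it does not by itself give power for the initiation hypothesis.

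In either case, replace the single power claim with a short table of detectable odds ratios over a plausible range of early-use prevalence, such as the one above, and state that the test is two-sided.

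Making problematic use, or age of initiation as an ordered variable, the main khat exposure is an option if early use proves rare. It is not needed to correct the statement.

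The cost is a restated figure that may look less favourable. Sample size, recruitment and data collection do not change.

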#### Case-finding

Following INTREPID methodology, building on our previous work [79] and arising from community engagement meetings, we will seek to identify people with potential psychosis through a combination of (1) proactive community-based case identification for those not in contact with care, and (2) case identification along help-seeking pathways. Proactive community-based case identification will comprise training of community health extension workers who carry out house-to-house visits for the 1000 households in their geographical catchment area, as well as other community informants, to identify people with possible psychosis. This approach has been shown to be sensitive for identification of people with psychosis in previous work by the Ethiopia team [29,95]. We will map out places where people with psychosis may seek help, including: health sector (specialist mental health services, general/primary healthcare services, health extension workers, private sector clinics); traditional and faith healing (churches, mosques, holy water sites, other healers); other sectors (police stations, prisons). We will identify focal persons (balanced by gender) in these sites and provide them with orientation and illustrated written materials in local languages. We will ask them to record contact details for any persons with features of psychosis who present to them and to inform the study team. The research team will receive referrals from focal persons and contact them proactively on a monthly basis to identify new presentations of people with possible psychosis. Descriptions of psychosis for both community-based identification and identification on help-seeking pathways will be informed by existing knowledge of local manifestations, extensive stakeholder consultation, including people with lived experience of psychosis, and emerging findings from the epidemiological study [92]. Data collectors will also regularly review health facility contact data supplemented by a registry implemented by the research team to identify people with psychosis.

Our approach to early case identification will be adapted for identification of people who are homeless and have psychosis, mapping out places where people who are homeless commonly congregate, liaising with community police and making contact early in the morning to facilitate privacy [92]. To further facilitate identification, we will also carry out awareness-raising and evidence-based stigma reduction activities in local communities, in collaboration with people with psychosis, and expanding local accessibility of mental health care through integration in primary health care using effective models for this setting [72,94].

